## Statistical analysis

### Sample size calculation

The sample size was calculated based on the expected reduction in serum NT-proBNP levels during the study. Previous studies showed that the prognosis of patients with an NT-proBNP level decrease by at least 30% from baseline through treatment is better than in those not treated [14, 15]. Therefore, according to another previous study on treating CHF with Chinese herbal medicine [4], the proportion of patients demonstrating a more than 30% decrease in NT-proBNP level in the placebo group is 31.98% (*P*
_1_ = 0.3198). According to previous clinical results, the investigators assumed that the proportion of patients demonstrating a more than 30% decrease in NT-proBNP level in the QSG group would be 53% (*P*
_2_ = 0.53). Given a type-I error rate of *α* = 0.05 and a type-II error rate of *β* = 0.2, and considering a dropout rate of approximately 20% among randomized patients, the investigators plan to include a total of 200 subjects. The relevant formulas are shown as follows:$$ \mathrm{n}={\left({\mathrm{Z}}_{1-\alpha /2}+{\mathrm{Z}}_{1-\beta}\right)}^2\times \left[{\mathrm{P}}_1\left(1-{\mathrm{P}}_1\right)+{\mathrm{P}}_2\left(1-{\mathrm{P}}_2\right)\right]/{\delta}_2 $$
$$ \mathrm{N}=2{\mathrm{n}}^{\ast}\left(1+20\%\right) $$

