## Randomization

An independent statistician who is unaware of the design and purpose of the study will generate a randomization table by using Statistical Analysis System (SAS, version 9.4). The 200 patients will be randomly allocated in a 1:1 ratio to either the QSG treatment group or the placebo group. The randomization will be stratified by study site. According to the design of the random program, the researcher will open one random envelope and obtain a randomization number for a patient on the day of inclusion. Both investigators and participants will be blind to the allocations.

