### Data analysis

Data entry and management will be completed by an independent data administrator to ensure data accuracy. A professional statistician will perform the data analysis for the results. We will use the intent-to-treat principle to analyze the efficacy and safety of QSG. For continuous variables, the independent two-sample Student’s *t* test will be used for comparisons between the two study groups, and the paired test will be used for intra-group comparisons. The *χ*2 test will be used for categorical variables. When continuous data distribution is not normal, the Wilcoxon test will be used. *P* < 0.05 is considered to be statistically significant, and all tests are two-tailed.

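### The 20% dropout allowance multiplies by 1.20 where its own definition calls for dividing by 0.80: a minor arithmetic error that leaves 200 patients slightly short of 80% power

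*Protocol article*

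**What the plan says.** The protocol article, under Sample size calculation, sets the error rates: "Given a type-I error rate of *α* = 0.05 and a type-II error rate of *β* = 0.2". It assumes that 31.98% of placebo patients and 53% of QSG patients reach a fall in NT-proBNP of more than 30%. It then reads: "considering a dropout rate of approximately 20% among randomized patients, the investigators plan to include a total of 200 subjects". Two formulas follow. The first is the two-proportion formula with unpooled variance, for n per arm. The second is N = 2n × (1 + 20%).

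Under Randomization: "The 200 patients will be randomly allocated in a 1:1 ratio". Under Data analysis: "The *χ*2 test will be used for categorical variables", and "all tests are two-tailed". The same section adopts the intention-to-treat principle, and the withdrawal paragraph under Eligibility, exclusion, and withdrawal criteria keeps rejected and withdrawn patients within the intention-to-treat set. Under Data collection and management, NT-proBNP is measured only at weeks 0 and 12.

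**The concern.** A dropout rate defined among randomised patients has the number randomised as its denominator. To keep 2n evaluable patients after losing 20% of N, one needs N × 0.80 = 2n, that is N = 2n/0.80. The printed formula takes 20% of the smaller, evaluable number and adds it, which gives too few. The definition and the formula in one paragraph therefore disagree, and the total of 200 rests on the formula.

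What is at stake is the type-II error stated for the primary outcome. If dropout runs at the planned rate, the chance of missing a true effect of the assumed size is somewhat larger than the protocol says.

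**Working it through.** **Inputs** (Sample size calculation unless noted)

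| Input | Value |
|---|---|
| Two-sided alpha | 0.05, z = 1.960 (two-tailed also in Data analysis) |
| Power | 0.80, z = 0.842 |
| Placebo responder rate P1 | 0.3198 |
| QSG responder rate P2 | 0.53 |
| Difference | 0.53 − 0.3198 = 0.2102 |
| Allocation | 1:1 (Randomization) |
| Dropout | about 20% of those randomised |
| Total N | 200 |

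**Step 1. Reproduce 200.** The denominator of the first formula is read as the squared difference; the printed 2 appears as a subscript, which is clerical and changes no number.

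n = (1.960 + 0.842)² × [0.3198 × 0.6802 + 0.53 × 0.47] / 0.2102² = 82.9, so 83 per arm.

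N = 2 × 83 × 1.20 = 199.2, so 200. The figure is reproduced. Pooled, continuity-corrected and one-sided variants, with either inflation, do not give 200, so its origin is clear.

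**Step 2. Apply the stated dropout.** 200 × 0.80 = 160, or 80 per arm. The formula requires 2 × 83 = 166. The shortfall is 6 evaluable patients.

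**Step 3. The inflation that fits the definition.** 2 × 83 / 0.80 = 207.5, so 208 (104 per arm), which is 8 patients or 4% more than 200.

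**Step 4. Dropout that 200 can absorb.** 166/200 = 83%, so 80% power by the printed formula holds up to 17% dropout.

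**Step 5. Power at 80 evaluable per arm.**

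- Printed (unpooled) formula: standard error = √[(0.3198 × 0.6802 + 0.53 × 0.47)/80] = 0.0764; 0.2102/0.0764 − 1.960 = 0.79; power 78.6%.
- Pooled variance under the null, as in the chi-square test: mean rate (0.3198 + 0.53)/2 = 0.4249; null standard error = √(2 × 0.4249 × 0.5751/80) = 0.0782; (0.2102 − 1.960 × 0.0782)/0.0764 = 0.75; power 77.2%.
- Exact binomial enumeration of the uncorrected chi-square test: 76.5%.

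**Step 6. Dependence on the analysis set** (pooled formula, N = 200)

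| Handling of the 20% who drop out | Rates compared | Per arm | Power |
|---|---|---|---|
| Left out of the comparison | 0.3198 vs 0.53 | 80 | 77.2% |
| Counted as non-responders (assumption, 20% in each arm) | 0.8 × 0.3198 = 0.256 vs 0.8 × 0.53 = 0.424 | 100 | 71.2% |
| All analysed, responding at the assumed rates | 0.3198 vs 0.53 | 100 | 85.8% |

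In the second case, raising N to 208 gives only 72.9%, so dividing by 0.80 is a full correction only when dropouts are left out.

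**The case against.** The strongest reply is about size. By the protocol's own formula the dropout arithmetic costs 1.4 points (78.6% against 80%). The dropout rate is given only as approximate, the responder rates are themselves assumptions, and 17% dropout would be covered. All of this stands.

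It is also fair that the further step from 78.6% to about 77% comes from matching the variance to the chi-square test. An unpooled planning formula ahead of a chi-square test is a standard approximation and not an error. The lower figure is useful when power is restated, but it should not be charged to the dropout formula.

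A third reply is that intention to treat keeps all 200 patients in the analysis, so nothing is lost. This stands only in part. It shows that the power depends on the analysis set, and the article does not say how a missing week-12 value is classified, which may be settled in an analysis plan that is not shown. But it does not rescue the 80%. The 85.8% needs every dropout to supply a response at the assumed rates, although NT-proBNP has no measurement between weeks 0 and 12. Counting dropouts as non-responders gives about 71%. And if nobody were lost to the primary comparison, the protocol would have no need of a dropout allowance.

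That the article condenses a longer protocol is no answer: the dropout definition, the formula and the total are all printed, and the definition does not fit the other two.

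**Conclusion.** The error is certain and minor. The allowance is defined among randomised patients but computed on evaluable ones. With 20% lost, 80 per arm remain against the 83 required, and power is 78.6% by the printed formula or about 77% for the uncorrected chi-square test, against 80% stated. These figures assume the protocol's responder rates, equal 20% dropout in both arms, and a primary comparison that leaves out patients without a week-12 NT-proBNP.

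A reader might infer that the trial is seriously underpowered, or that 200 patients fail to give 80% power under any analysis. The documents support neither. The shortfall is 1.4 points by the protocol's own method and about 3 points for the planned test, and with all 200 analysed at the assumed rates power would exceed 80%. The 71% figure rests on an assumed non-responder rule that the article does not state, so it is a reason to name the analysis set and not a finding about the design.

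**What to change.** Keep N = 200 and delete the second formula with its (1 + 20%) factor. Do not print 2n/0.80 as the source of N while keeping 200, because that formula yields 208 and the protocol would then contradict itself. Suggested wording:

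> With 200 patients randomised and 20% dropout, 80 patients per arm are evaluable. Power at two-sided alpha 0.05 for 31.98% against 53% is then about 77–79% (77% for the chi-square test, 79% by the formula above), provided that patients without a week-12 NT-proBNP are left out of the primary comparison. Keeping 80% power at 20% dropout would require 2 × 83/0.80 = 208 patients by the formula above.

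If the primary analysis will instead count dropouts as non-responders, state that and give about 71% in place of 77–79%.

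The cost is a few lines of text and a slightly less favourable stated power. No extra patients are needed. Under Trial status the article says that recruitment had not begun, so the statement can be corrected before any data exist. A sponsor who prefers to keep the 80% claim, on the completers basis and by the printed formula, would need 8 more patients.

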### Data analysis

Data entry and management will be completed by an independent data administrator to ensure data accuracy. A professional statistician will perform the data analysis for the results. We will use the intent-to-treat principle to analyze the efficacy and safety of QSG. For continuous variables, the independent two-sample Student’s *t* test will be used for comparisons between the two study groups, and the paired test will be used for intra-group comparisons. The *χ*2 test will be used for categorical variables. When continuous data distribution is not normal, the Wilcoxon test will be used. *P* < 0.05 is considered to be statistically significant, and all tests are two-tailed.

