The rejection and withdrawal criteria are listed as below: (1) unsuitability as judged by the investigators, (2) participants not following the protocol, (3) no visit record after treatment, and (4) voluntary withdrawal from the trial without any available data. These data will not be excluded from the study, instead, they will fall within ITT (intention-to-treat) through discussions among investigators, statisticians, data management, and others before un-blinding.

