### Placebo

The placebo group will receive placebo granules (13.6 g/pouch, twice per day—30 min after breakfast and dinner—for 12 weeks). The placebo is also manufactured by Beijing Tcmages Pharmaceutical Co., Ltd. (Beijing, China) by conforming to the specification for processing Chinese medicine in Beijing. The placebo granules are similar to the *Qishen* granules in appearance, taste, and smell.

All products will be packaged by Beijing Tcmages Pharmaceutical Co., Ltd. (Beijing, China). Either QSG or placebo pouches will be provided to each randomized participant at visit 1 (week 0 ± 3 days), visit 2 (week 4 ± 3 days), and visit 3 (week 8 ± 3 days).

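### Safety is assigned to intention-to-treat with patients lacking post-dose data kept in; if all randomized patients form the denominator, adverse-event rates in both arms are understated

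*Protocol article*

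**What the plan says.** The Data analysis section of the protocol article sets one principle for both halves of the objective: "We will use the intent-to-treat principle to analyze the efficacy and safety of QSG". It adds that the χ² "test will be used for categorical variables". It gives no separate denominator for AEs.

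The section on eligibility, exclusion and withdrawal lists four rejection or withdrawal categories. Two matter here: "no visit record after treatment" and "voluntary withdrawal from the trial without any available data". On how these cases are handled, it says: "These data will not be excluded from the study, instead, they will fall within ITT (intention-to-treat) through discussions among investigators, statisticians, data management, and others". The discussions take place before unblinding.

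Three other places bear on the point:

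- **Secondary outcomes:** safety rests on spontaneously reported events, vital signs and laboratory results.
- **Placebo:** "Either QSG or placebo pouches will be provided to each randomized participant at visit 1", so treatment is handed out at week 0.
- **Sample size calculation:** the total of 200 was reached "considering a dropout rate of approximately 20% among randomized patients".

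No set of exposed patients, and no grouping by treatment received, appears anywhere in the article.

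**The concern.** For a superiority comparison of efficacy, keeping every randomized patient is the usual choice, and counting a missing response as a failure is usually cautious. For harm the direction reverses. A patient in whom nobody looked for an AE cannot supply one, so counting that patient in the denominator lowers the observed rate and makes both treatments look safer than the data show.

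This is more than silence that an analysis plan could fill. The protocol names the principle for safety and elsewhere says that patients without post-treatment information belong to that population. An analysis plan that used an exposed set would depart from the published text.

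Safety is half of the stated objective, and the Discussion says that clinical-trial evidence on this product is still scarce. The AE rates from this trial are therefore likely to be quoted.

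**Working it through.** **The plan's own figure.** The point disputes no stated number, but the 20% should be read correctly before it is used. The sample size formula gives n = (1.960 + 0.842)² × [0.3198 × 0.6802 + 0.53 × 0.47] / 0.2102² = 82.9, so 83 per arm. Then N = 2 × 83 × 1.2 = 199.2, which rounds up to the stated 200. The 20% is therefore an inflation for loss to the NT-proBNP responder comparison, which needs a week-12 sample. It is not an estimate of the share of patients without safety data.

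**Inputs**

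- Randomized per arm: 100, from "The 200 patients will be randomly allocated in a 1:1 ratio to either the QSG treatment group or the placebo group".
- r, the true AE risk: not in the documents; 10% and 30% are used as examples.
- u, the share of an arm without post-dose safety data: not in the documents. The assumed range is 2% to 10%, with 20% as a ceiling that treats every planned dropout as having no safety data.
- AE risk is assumed to be the same in patients with and without safety data.

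**Dilution of a rate.** If all randomized patients are in the denominator, observed rate = r × (1 − u).

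| u | true 10% reads | true 30% reads |
|---|---|---|
| 2% | 9.8% | 29.4% |
| 5% | 9.5% | 28.5% |
| 10% | 9.0% | 27.0% |
| 20% (ceiling) | 8.0% | 24.0% |

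The relative understatement equals u.

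**Effect on the comparison.** With the same u in both arms, the risk difference becomes (r₁ − r₂)(1 − u), and the risk ratio r₁/r₂ does not change. For assumed risks of 25% and 10% with u = 10%, the observed rates are 22.5% and 9.0%. The difference is 13.5 points instead of 15, and the ratio is 2.5 either way. Power to detect the difference is 74.9% with 100 per arm and diluted rates, against 75.9% with the 90 per arm who have data.

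**An AE never seen.** With zero events in n patients, the one-sided 95% upper bound is 1 − 0.05^(1/n).

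- n = 100: 2.95%
- n = 90: 3.27%
- n = 80: 3.68%

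Quoting the bound on 100 when only 90 or 80 patients were observed overstates how much risk has been excluded.

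**The case against.** The strongest reply is that the dilution is not written into the protocol. Data analysis names a principle and a test; it does not say that patients without data count as free of events. The withdrawal section leaves these cases to a discussion before unblinding, and an analysis plan not shown here may settle the denominator. This stands as far as it goes, so the point has to be conditional: the bias arises if AE proportions are taken over all randomized patients. It does not remove the point, because the stated population invites that calculation and no other safety population is offered.

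Several stronger readings are tempting, and the documents do not support them:

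- **A reader might infer that a fifth of patients will have no safety data.** The 20% covers all dropout from a week-12 endpoint. Visits occur every four weeks and AEs are monitored continuously, so a patient who leaves after week 4 or week 8 still has post-dose safety information.
- **A reader might infer that many randomized patients will never be exposed.** Dispensing at visit 1 suggests that they will be few.
- **A reader might infer that the plan favours QSG in particular.** The dilution acts on both arms. Only unequal loss would distort the risk ratio, and nothing in the documents points to unequal loss.
- **A reader might infer that harms will be credited to the wrong arm through dispensing errors.** Packs are labelled with random codes and dispensed by randomization number, and no section suggests misallocation.

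A further objection also stands. A set defined only by taking at least one dose would not cure the dilution, because a treated patient with no later visit would remain in it. The fix therefore has to deal with post-dose contact as well.

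**Conclusion.** The point holds in conditional form and is minor. The protocol assigns safety to intention-to-treat, keeps patients without post-dose data in that population, and names no exposed safety set. If AE proportions use all randomized patients, rates in both arms and the risk difference shrink by (1 − u).

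The size cannot be derived from the documents. It is a relative understatement of 2% to 10% over the assumed range of u and 20% at the ceiling. The loss of power for a between-arm AE comparison is about one percentage point in the example above. These figures assume equal risk in observed and unobserved patients. If patients who vanish have more AEs, the understatement is larger and no choice of denominator fully repairs it, which is why their number should be shown.

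**What to change.** Replace the single sentence in Data analysis with wording to this effect:

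- Efficacy, including composite cardiac events, is analysed by intention-to-treat.
- Safety is analysed in patients who took at least one dose, grouped by the treatment they received.
- AE and serious AE proportions are calculated over those patients with any post-dose safety contact. A visit, a laboratory result or a spontaneous report each counts as contact.
- For each arm, the number of treated patients without such contact and the number never dosed are reported.

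The withdrawal section should then say that its rule on keeping patients in the intention-to-treat set concerns efficacy. Exposure-adjusted rates are optional, since the article does not say that exposure time is recorded.

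The cost is a few sentences and one more table. The article states that recruitment had not begun, so the change could be made before any data exist. The downside is that AE rates may look slightly less favourable than under the present wording.

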## Data collection and management

A CRF will be used for each participant to collect relevant data. The participants will be evaluated every 4 weeks during the study. Data on CCEs, NYHA functional classification, 6MWD, patient quality of life and the TCM syndrome integral scale will be collected at each visit (week 0 ± 3 days, week 4 ± 3 days, week 8 ± 3 days, and week 12 ± 3 days). The NT-proBNP and LVEF will be measured only at the first and the last visit (week 0 ± 3 days and week 12 ± 3 days). The Standard Protocol Items: Recommendations for Interventional Trials (SPIRIT) flowchart of the trial can be found in Fig. 2.

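### Continuous secondary outcomes get unadjusted between-arm tests, valid but imprecise, and within-arm paired tests at the same 0.05 level that do not estimate a QSG effect

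*Protocol article*

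**What the plan says.** The protocol article, Data analysis, sets one rule for every continuous variable. The rule, which refers to the unpaired t test, is: "test will be used for comparisons between the two study groups, and the paired test will be used for intra-group comparisons". The fallback is: "When continuous data distribution is not normal, the Wilcoxon test will be used". The criterion for all of these is P "< 0.05 is considered to be statistically significant, and all tests are two-tailed". No baseline covariate, site term or repeated-measures model is named. The paired tests are not marked as descriptive.

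The design supplies what an adjusted analysis would need. Data collection and management states: "Data on CCEs, NYHA functional classification, 6MWD, patient quality of life and the TCM syndrome integral scale will be collected at each visit", that is, at weeks 0, 4, 8 and 12. It adds: "The NT-proBNP and LVEF will be measured only at the first and the last visit", at weeks 0 and 12. The Randomization section stratifies by study site.

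The continuous secondary outcomes are therefore 6MWD, quality of life and TCM score (four visits each) and LVEF (two visits). NYHA class and composite cardiac events are not continuous and fall outside this point.

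**The concern.** There are two separate issues.

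**Precision.** A patient's baseline value usually predicts the week-12 value, and site was thought important enough to stratify on. A two-sample test without covariates leaves that explained variation in the error term. The confidence interval for the randomized comparison is then wider than the data require.

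**Within-arm tests.** A paired test asks whether one arm changed from its own baseline. Both arms receive guideline therapy, which may be adjusted in serious cases, and entry requires LVEF of 40% or less. Background care, repeated testing or regression to the mean can therefore move both arms without any QSG effect. Because the paired tests share the 0.05 criterion with the randomized comparison, a result that is significant on QSG and not on placebo could be reported as efficacy. That pattern says little about the difference between the arms.

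**Working it through.** **1. The plan's own figure.** Inputs from Sample size calculation: "decrease in NT-proBNP level in the placebo group is 31.98"%; "decrease in NT-proBNP level in the QSG group would be 53"%; two-sided α = 0.05; β = "0.2, and considering a dropout rate of approximately 20% among randomized patients". The δ term is read as δ squared.

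n = (1.960 + 0.842)² × [0.3198 × 0.6802 + 0.53 × 0.47] / (0.53 − 0.3198)² = 82.9, so 83 per arm.

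N = 2 × 83 × 1.2 = 199.2, so 200. The stated size reproduces. It concerns the binary primary outcome only. The article gives no SD, correlation or power for any continuous outcome.

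**2. Precision of the between-arm comparison.** Assumptions: 100 randomized per arm less 20% dropout leaves 80 completers per arm; the SD is equal at baseline and week 12; the correlation is ρ. The article does not say whether the t test compares week-12 values or changes, so both are shown. Relative to a t test on week-12 values (variance 1):
- change-score t test: 2(1 − ρ)
- ANCOVA on baseline: 1 − ρ²
- ANCOVA relative to change score: (1 − ρ²) / [2(1 − ρ)] = (1 + ρ)/2

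The difference detectable with 80% power by a week-12 t test is (1.960 + 0.842) × √(2/80) = 0.443 SD. The other detectable differences are 0.443 times the square root of the variance ratio.

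| ρ (assumed) | ANCOVA / week-12 t test | ANCOVA / change-score t test | Detectable, change score | Detectable, ANCOVA |
|---|---|---|---|---|
| 0.3 | 0.91 | 0.65 | 0.524 SD | 0.423 SD |
| 0.5 | 0.75 | 0.75 | 0.443 SD | 0.384 SD |
| 0.6 | 0.64 | 0.80 | 0.396 SD | 0.354 SD |
| 0.7 | 0.51 | 0.85 | 0.343 SD | 0.316 SD |
| 0.8 | 0.36 | 0.90 | 0.280 SD | 0.266 SD |

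ANCOVA has the smaller variance under both readings. At ρ = 0.5 to 0.7, its 95% CI is 13% to 29% narrower than that of the week-12 t test (√0.75 = 0.87, √0.51 = 0.71), and 13% to 8% narrower than that of the change-score test (√0.75 = 0.87, √0.85 = 0.92). The ratios refer to t tests. The further gain from the site term is not quantified.

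**3. Within-arm tests when QSG has no effect.** Assume that both arms improve by the same c SD, with n = 80 per arm. The SD of change is √[2(1 − ρ)], and the paired test has noncentrality c√n / √[2(1 − ρ)]. If p is the chance that one arm is significant, then QSG alone is significant with probability p(1 − p), and exactly one arm with probability 2p(1 − p).

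For c = 0.2 and ρ = 0.5: SD of change = 1; noncentrality = 0.2 × √80 = 1.789; p = Φ(1.789 − 1.960) + Φ(−1.789 − 1.960) = 0.432. QSG alone: 0.432 × 0.568 = 0.245. Exactly one arm: 0.491.

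| c (SD) | ρ | p, each arm | QSG alone | Exactly one arm |
|---|---|---|---|---|
| 0.1 | 0.5 | 0.145 | 0.124 | 0.249 |
| 0.2 | 0.5 | 0.432 | 0.245 | 0.491 |
| 0.3 | 0.5 | 0.765 | 0.180 | 0.359 |
| 0.5 | 0.5 | 0.994 | 0.006 | 0.012 |
| 0.1 | 0.7 | 0.211 | 0.167 | 0.333 |
| 0.2 | 0.7 | 0.637 | 0.231 | 0.463 |
| 0.3 | 0.7 | 0.934 | 0.062 | 0.124 |

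Since p(1 − p) cannot exceed 0.25, the 0.2 SD case is close to the worst for a one-arm-only result. With larger common improvement both arms become significant. The QSG before-after test is then almost always positive (0.994 at 0.5 SD, ρ = 0.5) although there is no treatment effect.

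**The case against.** The best reply is that the between-arm test is sound. Under randomization an unadjusted two-sample comparison holds its type I error, so the choice affects efficiency, and only for secondary outcomes. That stands. It can also be said that covariates and models are often left to an analysis plan that is not shown. That does not answer this point, because the article names the tests it will use.

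On the paired tests, nothing in the article offers a within-arm change as evidence of efficacy, and the primary outcome is defined against placebo. That also stands: the misreading is a risk the wording leaves open, not a stated intention. The assumed common improvement is open to challenge too. Patients must be clinically stable on fixed doses for at least 2 weeks, and the 31.98% placebo responder rate comes from another study and a different outcome, so it does not establish a mean improvement in these scales.

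A reader might also infer more than the text supports:
- **That every outcome is tested at every visit, with a large family-wise error.** The visit schedule describes data collection. No week is named for any test, and repeated measures on the same patients would not be independent.
- **That early visits of dropouts are thrown away.** The article does not say so. It states the intent-to-treat principle and says data of withdrawn patients will not be excluded.
- **That baseline is ignored.** If the t test is on changes, baseline is used, though less efficiently than by ANCOVA.

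**Conclusion.** The point holds in limited form. The stated between-arm test for 6MWD, quality of life, TCM score and LVEF is valid but gives up precision that the collected baseline would supply. At an assumed correlation of 0.5 to 0.7, ANCOVA would need 75% to 51% of the variance of a week-12 t test, or 75% to 85% of that of a change-score test. The size depends on the correlation, which the article does not give, and on equal SDs at the two visits. The direction is the same across the range shown.

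The within-arm paired tests share the 0.05 criterion but do not estimate a QSG effect. With no effect and an equal 0.2 SD improvement in both arms, they would separate the arms about 49% of the time, with QSG alone significant in about 25%. Those two figures are near their maximum and rest on the assumed improvement, 80 completers per arm and correlation 0.5. The binary primary outcome, its chi-square test and N = 200 are not touched.

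**What to change.** In Data analysis, replace the rule for continuous outcomes with the following:
- **LVEF:** ANCOVA of the week-12 value, adjusted for baseline and site.
- **6MWD, quality of life, TCM score:** for each, a mixed model for repeated measures with baseline, site, visit, arm and arm-by-visit interaction.
- **Reported result:** the week-12 between-arm difference with its 95% CI.
- **Within-arm changes:** descriptive only, without P values.

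The cost is a change of wording and slightly more programming. No new data, visits or patients are needed, and recruitment had not begun when the article was written.
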